## Abstract

**Background:**

Alternative evidence-based cardiac rehabilitation (CR) delivery models that overcome significant barriers to access and delivery are needed to address persistent low utilization. Models utilizing contemporary digital technologies could significantly improve reach and fidelity as complementary alternatives to traditional center-based programs.

**Objective:**

The aim of this study is to compare the effects and costs of the innovative *Smartphone Cardiac Rehabilitation, Assisted self-Management* (SCRAM) intervention with usual care CR.

**Methods:**

In this investigator-, assessor-, and statistician-blinded parallel 2-arm randomized controlled trial, 220 adults (18+ years) with coronary heart disease are being recruited from 3 hospitals in metropolitan and regional Victoria, Australia. Participants are randomized (1:1) to receive advice to engage with usual care CR or the SCRAM intervention. SCRAM is a 24-week dual-phase intervention that includes 12 weeks of real-time remote exercise supervision and coaching from exercise physiologists, which is followed by 12 weeks of data-driven nonreal-time remote coaching via telephone. Both intervention phases include evidence- and theory-based multifactorial behavior change support delivered via smartphone push notifications. Outcomes assessed at baseline, 12 weeks, and 24 weeks include maximal aerobic exercise capacity (primary outcome at 24 weeks), modifiable cardiovascular risk factors, exercise adherence, secondary prevention self-management behaviors, health-related quality of life, and adverse events. Economic and process evaluations will determine cost-effectiveness and participant perceptions of the treatment arms, respectively.

**Results:**

The trial was funded in November 2017 and received ethical approval in June 2018. Recruitment began in November 2018. As of September 2019, 54 participants have been randomized into the trial.

**Conclusions:**

The innovative multiphase SCRAM intervention delivers real-time remote exercise supervision and evidence-based self-management behavioral support to participants, regardless of their geographic proximity to traditional center-based CR facilities. Our trial will provide unique and valuable information about effects of SCRAM on outcomes associated with cardiac and all-cause mortality, as well as acceptability and cost-effectiveness. These findings will be important to inform health care providers about the potential for innovative program delivery models, such as SCRAM, to be implemented at scale, as a complement to existing CR programs. The inclusion of a cohort comprising metropolitan-, regional-, and rural-dwelling participants will help to understand the role of this delivery model across health care contexts with diverse needs.

**Trial Registration:**

Australian New Zealand Clinical Trials Registry (ACTRN): 12618001458224; anzctr.org.au/Trial/Registration/TrialReview.aspx?id=374508.

**International Registered Report Identifier (IRRID):**

DERR1-10.2196/15022

## Introduction

### Background

Cardiac rehabilitation (CR) is a cost-effective multifactorial intervention that plays a critical role in the secondary prevention of coronary heart disease (CHD) [1-4]; however, low rates of participation in traditional center-based programs (ie, face-to-face delivery) [5] continue to limit impact on individual, clinical, and economic outcomes. Uptake and adherence to center-based CR are influenced by diverse factors, but access barriers such as limited program availability, transport restrictions, conflicting domestic/occupational responsibilities, and geographic isolation are key contributors [6-9]. Establishing new programs in diverse locations could improve accessibility, but this may not be feasible, given the high infrastructure costs associated with center-based facilities [10,11]. The traditional CR paradigm cannot meet the needs of many eligible individuals, and complementary alternatives that deliver evidence-based support outside of face-to-face settings are urgently needed to complement current services.

Home-based delivery overcomes many access barriers and can have comparable short-term effects on mortality, exercise capacity, and health-related quality of life [12], but it often lacks oversight and guidance from CR professionals, which are central to best-practice center-based programs.

Rapid advances in mobile communications and wearable sensor technologies could bridge the gap between home- and center-based delivery models by combining near-universal accessibility with responsive individualized clinical oversight. CR delivered via landline telephone, SMS, and Web-based mechanisms has demonstrated promising potential [13]. However, few interventions have incorporated emerging digital technologies that can support more comprehensive, responsive, and interactive intervention delivery that emulates center-based support [14]. We previously developed a 12-week exercise-based mobile health (mHealth) intervention, named Remote Exercise MOnitoring Trial for Exercise-based Cardiac Rehabilitation (REMOTE-CR), to address this unmet need [15]. Using mobile, Web, and wearable sensor technologies, our bespoke intervention remotely connected participants with exercise physiologists to receive real-time individualized supervision and coaching during exercise training from any geographic location with a local or mobile internet connection. In a noninferiority randomized controlled trial (RCT), we showed that the effect of REMOTE-CR on functional capacity was as good as traditional center-based programs. The trial also demonstrated comparable effects on modifiable cardiovascular risk factors and motivational outcomes, substantial program delivery cost savings via reduced infrastructure requirements, as well as high usability, acceptability, and end-user demand for REMOTE-CR as a usual care service [10,16]. Collectively, these findings suggest complementing existing center-based programs with effective mHealth delivery models could increase overall engagement with CR by allowing more individuals to access individualized intervention support.

However, REMOTE-CR trial findings also identified opportunities for further development. First, REMOTE-CR focused primarily on exercise training, whereas comprehensive CR should also incorporate health behavior change and education, management of other lifestyle risk factors—including healthy diet and tobacco smoking—and adherence to prescribed medications [2,3]. Second, the advantages of mHealth CR are likely to be greatest in regional and rural areas where access to existing services is lowest [17]; however, the predominantly urban sample in our trial meant we could not determine impact in regional or rural areas. Third, long-term maintenance of self-management behaviors is a key component of CR [2,3], and—in combination with substantial cost-efficiencies [10,18,19]—near-universal accessibility makes mHealth CR well suited for supporting long-term self-management. However, our REMOTE-CR intervention provided only 12 weeks of support. Fourth, our previous trial actively facilitated referral and priority enrollment into center-based rehabilitation for participants randomized to the control group. This differs from usual care practice as referral rates are far from optimal [20,21], and individuals are typically required to self-initiate engagement with usual care services.

We have subsequently developed a 24-week multifactorial intervention (*Smartphone Cardiac Rehabilitation, Assisted self-Management * [SCRAM]) that addresses previous participant feedback [16], includes more comprehensive multifactorial behavior change support, and integrates an additional 12-week maintenance phase to assist participants’ transition toward self-determined long-term adherence to self-management behaviors.

### Objectives

This protocol describes the rationale and design of a multicenter RCT that aims to compare the effects and costs of SCRAM on modifiable cardiovascular risk factors with usual care CR among urban-, regional-, and rural-dwelling individuals with CHD. Usual care CR was chosen as the comparator as it is the standard of care. We hypothesize that the effects of SCRAM on primary and secondary outcomes will be superior to usual care CR alone and that SCRAM will be cost-effective.

## Methods

### Design

A multicenter investigator- and assessor-, and statistician-blinded parallel 2-arm RCT is being conducted to compare effects of SCRAM and usual care CR on maximal aerobic exercise capacity, modifiable cardiovascular risk factors, and self-management behaviors (Figure 1). Process and economic evaluations aim to determine participants’ perceptions of the SCRAM and usual care programs and the cost-effectiveness of SCRAM, respectively.

The trial protocol was prospectively registered with the Australian New Zealand Clinical Trials Registry (ACTRN12618001458224) on August 30, 2018, and it adheres to the Standard Protocol Items: Recommendations for Interventional Trials 2013 statement [22]. The intervention has been described according to recommendations in the Template for Intervention Description and Replication and Consolidated Standards of Reporting Trials (CONSORT; electronic health [eHealth] extension) statements (Multimedia Appendices 1-3). Reporting of trial outcomes will adhere to the CONSORT statement and its eHealth extension [23-25].

**Figure 1 figure1:**
[figure not shown]
Consolidated Standards of Reporting Trials design schematic. CR: cardiac rehabilitation; SCRAM: Smartphone Cardiac Rehabilitation, Assisted self-Management.

### Setting

The trial is being conducted at 1 metropolitan (Sunshine Hospital, Western Health) and 2 regional (University Hospital Geelong, Barwon Health; Bendigo Hospital, Bendigo Health) health care providers in Victoria, Australia. These trial centers collectively serve approximately 1.5 million individuals and provide acute coronary care services to individuals living in large regional and rural catchment areas across Northern and Western Victoria. This enables sampling of a geographically diverse cohort that includes metropolitan-, regional-, and rural-dwelling participants, which is particularly important as age-standardized rates of CHD hospitalizations and access to traditional center-based CR are worse outside metropolitan areas in Australia [26,27].

We anticipate recruiting equal numbers of participants via each trial center; a priori prediction of the ratio of metropolitan, regional, and rural participants is not possible, but it will be reported together with trial outcomes.

### Recruitment

Recruitment began at all trial centers on November 12, 2018, and it is monitored via monthly reporting to the trial steering group, comprising the trial investigators. Research nurses identify eligible individuals before hospital discharge and via outpatient cardiac clinics, provide potential participants with trial information and consent forms, obtain consent to refer interested individuals to the research team, and document reasons for declining participation. A researcher subsequently confirms individuals’ interest in the trial, answers unresolved questions, and schedules baseline assessment appointments for those who volunteer to participate.

### Eligibility

Eligible participants are adults (18+ years) with recently diagnosed CHD (angina, myocardial infarction, and coronary revascularization within the previous 6 months), who are clinically stable outpatients (no CHD-related hospitalization within 6 weeks of baseline assessment) and can understand and write English. Participants are excluded if they have New York Heart Association class III/IV heart failure, terminal disease, significant non-CHD exercise limitations, or contraindications for maximal exercise testing. Participants with an implanted pacemaker or automated defibrillator are excluded because of wearable sensor manufacturer recommendations. Smartphone ownership is not required; participants are lent a smartphone for the duration of the intervention period if required. Participants who cannot complete baseline primary outcome assessment are ineligible for randomization, and participants who experience exercise-induced medical complications may be ineligible, pending referral for medical assessment and approval.

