### Randomization

Upon completion of baseline data collection, participants are randomized at a 1:1 ratio to receive 24 weeks of usual care CR alone (control) or the 24-week SCRAM program (intervention). Treatment allocation follows a computer-generated schedule prepared by a biostatistician who is not involved in recruitment, treatment allocation, or outcome assessment; the randomization schedule is stratified by sex and trial center and uses random permuted blocks (n=2 and 4). A centralized Web-based randomization system (Research Electronic Data Capture [REDCap]; Vanderbilt University) ensures allocation concealment until the time of randomization. Access to the randomization schedule is restricted to the blinded trial biostatistician. The trial steering group is permitted access to summarized allocation progress data to monitor recruitment. Researchers undertaking data collection have no access to the randomization schedule other than to retrieve participants’ concealed treatment allocation at baseline assessments.

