#### Statistical Analysis

Baseline characteristics will be summarized descriptively for the full sample and by treatment group. A linear regression model—adjusted for baseline values and stratification variables—will be fitted to assess the primary outcome. Primary analyses will be performed on the principle of intention to treat. Assuming there is a reasonable amount (>5%) of missing data, primary analyses will be conducted using multiple imputation, imputing all outcomes using a single (joint) imputation model. Imputation models will include participant age, sex, type of diagnosis (eg, angina, myocardial infarction, and coronary revascularization), in addition to any other covariates that appear to predict missingness. A per-protocol analysis will be conducted with complete cases to test the robustness of treatment effects under different assumptions. Preplanned subgroup analyses will be conducted to determine treatment effects by levels of treatment adherence, sex, and trial center (Figure 1). Secondary analyses will adjust the regression model for baseline prognostic factors, including age, sex, and employment status.

A similar approach will be used to assess continuous secondary outcomes (Table 3); logistic regression will be used for binary outcomes. Model-adjusted estimates and group differences will be reported with 95% CIs and probability values. All statistical tests will be 2-sided at α=.05. The biostatistician will remain blinded throughout the analysis of treatment effects. A detailed statistical analysis plan will be developed before the completion of data collection to guide analyses.

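### The primary VO2max model leaves out age, which the plan itself calls prognostic and collects at baseline; adding it would be a cheap but modest gain in precision

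*Protocol article*

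**What the plan says.** The Statistical Analysis section fixes the primary model: "A linear regression model—adjusted for baseline values and stratification variables—will be fitted to assess the primary outcome". The Randomization section supplies the stratification variables: "the randomization schedule is stratified by sex and trial center". The primary covariates are therefore baseline VO2max, sex and center.

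The same Statistical Analysis section then adds: "Secondary analyses will adjust the regression model for baseline prognostic factors, including age, sex, and employment status". Age appears once more, for handling missing data: "Imputation models will include participant age, sex, type of diagnosis". Table 3 lists age among the sociodemographic characteristics collected at week 0.

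The Eligibility section admits patients with "recently diagnosed CHD (angina, myocardial infarction, and coronary revascularization within the previous 6 months". Diagnosis type is named for the imputation model but not for the primary model.

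**The concern.** When a covariate is known at baseline, is expected to predict the outcome and is prespecified, putting it in the primary linear model usually narrows the confidence interval for the treatment effect and corrects for chance imbalance. In a randomized comparison it does so without introducing bias. The plan identifies age as such a covariate and collects it, yet leaves it out of the analysis on which the trial is judged. Randomization is not stratified by age. If the arms happen to differ in age, the trial would report two differently adjusted estimates, and the primary one would be the one without the correction.

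There is also a wording defect. The secondary model is described as adjusting for age, sex and employment status. Sex is already in the primary model as a stratification variable, so of the three named factors only age and employment status are new.

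At stake is a small amount of precision on the primary endpoint, together with clarity about what the secondary analysis adds.

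**Working it through.** **Inputs.** From the Sample Size section: difference 2.0, SD 6.75, correlation 0.80 between repeated measures, two-sided α 0.05, 90% power, 174 evaluable, 220 randomized, 20% loss. From the Randomization section: 1:1 allocation, three centers and two sexes as strata. Not in the documents: the share R² of residual variance that age or diagnosis explains once baseline VO2max, sex and center are in the model. It is assumed below and shown as a range.

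**Step 1: reproduce the plan's figure.** Residual SD after baseline adjustment = 6.75 × √(1 − 0.80²) = 6.75 × 0.60 = 4.05. Participants per arm = 2 × [(1.960 + 1.282) × 4.05 / 2.0]² = 86.2, rounded up to 87, so 174 in total. This matches. Allowing for 20% loss, 174 / 0.80 = 217.5, so 218, consistent with the stated 220. The sample size thus already relies on baseline adjustment, which removes 64% of the outcome variance. Any further covariate acts only on the remaining 36%.

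**Step 2: base case.** With 20% loss from 220, 176 are analysed, 88 per arm. SE = 4.05 × √(2/88) = 0.611. Power = Φ(2.0/0.611 − 1.96) = Φ(1.316) = 90.6%.

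**Step 3: cost of extra terms.** The planned model has six parameters (intercept, treatment, baseline, sex, two for center), leaving 176 − 6 = 170 residual degrees of freedom. Adding k covariates inflates the variance of the treatment effect by about 169/(169 − k): 1.006 for one term, 1.018 for three, 1.024 for four.

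**Step 4: net effect of age alone (k = 1).** SE = 0.6106 × √[(1 − R²) × 1.006].

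| Assumed R² | SE | Power |
|---|---|---|
| planned model | 0.611 | 90.6% |
| 1% | 0.609 | 90.7% |
| 3% | 0.603 | 91.2% |
| 5% | 0.597 | 91.8% |

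The break-even R² is 1 − 168/169 = 0.6%.

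**Step 5: age plus two diagnosis terms (k = 3).** The break-even R² is 1 − 166/169 = 1.8%. At a joint R² of 2% power is 90.6% (no visible change), at 5% about 91.5%, and at 10% about 92.8%.

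**Step 6: a larger set of four terms (k = 4).** At a joint R² of 2% power is 90.5%, so there is no net gain. Extra covariates pay only if they predict the outcome.

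**The case against.** The strongest reply is that nothing here is wrong. The primary model is prespecified, unbiased and consistent with the randomization, and it reaches the stated 90% power without further covariates. An age-adjusted analysis is already planned, the word "including" in that sentence leaves its covariate list open, and age and diagnosis both support the imputation. Which adjusted model is called primary is partly a matter of preference, and baseline VO2max already does most of the work. All of this stands, and it limits the point to an optional improvement.

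Three stronger readings are tempting and are not supported.

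- A reader might infer that participants enter anywhere from 6 weeks to 6 months after their event, so that time since event belongs in the model. The Eligibility section sets no such lower limit. Its condition is "no CHD-related hospitalization within 6 weeks of baseline assessment", so a patient with angina who was not hospitalized could enter sooner. Time from index event is also undefined for angina without an acute event, and the article does not show that an analysable date is recorded.
- A reader might call the extra precision free. Step 6 shows that it is not.
- A reader might conclude that the trial is underpowered or its primary analysis flawed. Step 1 shows that the sample size and the model agree.

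What survives the objection is that the plan's own classification of age as prognostic sits oddly with its exclusion from the primary model, and that sex is listed redundantly.

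**Conclusion.** The point holds as a cheap improvement in precision, not as an error. For age alone, at 88 analysed per arm, power moves from 90.6% to between about 90.7% and 91.8% if age explains 1% to 5% of the residual variance. That range is an assumption, because the documents give no figure, and below about 0.6% there is no gain. The calculation also takes SD 6.75, correlation 0.80 and 20% loss as planned, and treats the analysis as one of 176 observed participants rather than modelling the multiple imputation. Diagnosis type is a reasonable optional addition. A time-since-event covariate is not supported by what the article shows. The duplicate listing of sex is a wording matter that affects no estimate.

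**What to change.** In the Statistical Analysis section, and in the analysis plan that the article says will be written before data collection ends:

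1. Prespecify, before unblinding, that the primary linear model adjusts for baseline VO2max, sex, trial center and age. Optionally add the diagnosis type already named for the imputation model, with its categories defined in advance, since one patient may have had both infarction and revascularization.
2. Keep the model with baseline VO2max, sex and center as a sensitivity analysis.
3. Delete sex from the factors added in the secondary model. With age moved to the primary model, employment status is the one remaining named addition.

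The imputation model already includes age, sex and diagnosis type, so it needs no change for these covariates. The cost is a wording change and one degree of freedom for age, or three with two diagnosis terms, out of about 170. No new data collection is needed for age. Diagnosis data come from hospital records where possible, so their completeness should be checked before diagnosis is included.

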### Randomization

Upon completion of baseline data collection, participants are randomized at a 1:1 ratio to receive 24 weeks of usual care CR alone (control) or the 24-week SCRAM program (intervention). Treatment allocation follows a computer-generated schedule prepared by a biostatistician who is not involved in recruitment, treatment allocation, or outcome assessment; the randomization schedule is stratified by sex and trial center and uses random permuted blocks (n=2 and 4). A centralized Web-based randomization system (Research Electronic Data Capture [REDCap]; Vanderbilt University) ensures allocation concealment until the time of randomization. Access to the randomization schedule is restricted to the blinded trial biostatistician. The trial steering group is permitted access to summarized allocation progress data to monitor recruitment. Researchers undertaking data collection have no access to the randomization schedule other than to retrieve participants’ concealed treatment allocation at baseline assessments.

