### Blinding

Primary outcome assessment will be blinded; participants are blinded at baseline (ie, prerandomization) but cannot be blinded thereafter because of the nature of the treatments. A trial investigator who is not involved with data collection may be unblinded to participants’ treatment allocation if it is medically necessary. The biostatistician will remain blinded to treatment allocation throughout the analysis of trial outcomes.

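### The randomization schedule is held by the biostatistician who is said to be blinded, so the stated statistician blinding is not assured as written

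*Protocol article*

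**What the plan says.** The Abstract and the Design section make statistician blinding part of the trial's description; Design reads "A multicenter investigator- and assessor-, and statistician-blinded parallel 2-arm RCT is being conducted". The Blinding section adds: "The biostatistician will remain blinded to treatment allocation throughout the analysis of trial outcomes". The Statistical Analysis section repeats the commitment: "The biostatistician will remain blinded throughout the analysis of treatment effects".

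The Randomization section describes who makes and who holds the allocation list. It is "prepared by a biostatistician who is not involved in recruitment, treatment allocation, or outcome assessment". On custody it says: "Access to the randomization schedule is restricted to the blinded trial biostatistician".

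Two lesser forms of access appear in the same section. The steering group may see summarized allocation progress. For the outcome staff, "Researchers undertaking data collection have no access to the randomization schedule other than to retrieve" an individual participant's concealed allocation at baseline. Neither is access to the whole list.

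**The concern.** A person who can open the allocation list can learn any participant's arm. The article gives that access to a role it calls blinded in the same sentence, and elsewhere promises that the biostatistician stays blinded until the analysis is finished. Both cannot hold unless some arrangement exists that the article does not describe.

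Two things are at stake. First, some analysis choices are left to judgment, and an analyst who knows the arms could be influenced by that knowledge, even without intent. Second, the trial will be reported as statistician-blinded, and readers will give that label weight. A label that the access rule undercuts should not be carried into the report.

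**Working it through.** No formula applies: the point depends on no effect size, variance, error rate or sample size. The check sets the statements side by side.

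**Step 1. Which role is blinded, and which holds the list?**

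| Section | Role | What is stated |
|---|---|---|
| Abstract, Design | statistician | blinded |
| Blinding | the biostatistician | blind to allocation during analysis of outcomes |
| Statistical Analysis | the biostatistician | blind during analysis of treatment effects |
| Randomization | a biostatistician | prepares the schedule; excluded from three activities, analysis not among them |
| Randomization | the blinded trial biostatistician | sole access to the schedule |

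The label on the last row matches the role in the second and third rows. Read as written, the analyst holds the list.

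**Step 2. Does the text offer a way out?** Three arrangements would reconcile the rows: a second, unblinded statistician; a schedule showing only coded arms; or a separate key holder. The article mentions none of them. If there are two statisticians, the custody sentence names the wrong one and still needs correcting.

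**Step 3. Which analysis choices could knowledge of the arms affect?** From the Statistical Analysis section:

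- *Fixed:* linear regression adjusted for baseline value and stratification variables; intention to treat; one joint imputation model; age, sex and type of diagnosis in that model; imputation when more than 5% of data are missing.
- *Open in the article:* which further covariates enter the imputation model as predictors of missingness, and who belongs to the per-protocol set.

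The 5% rule is a count and does not depend on knowing the arms. It is likely to be met. The Sample Size section allows for 20% loss; 20% of 220 is 44 participants, against a threshold of 5% of 220, which is 11. If so, imputation becomes the primary approach and the choice of extra covariates is a live one. The per-protocol set affects a robustness analysis, not the primary result.

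**Step 4. Would a masked arm code be enough for every analysis?** Not for all. The Process Evaluation section measures SCRAM fidelity from recorded exercise sessions, compliance with notifications and platform usage, and usual-care fidelity from self-reported uptake. Session and platform records arise only in the SCRAM arm. With a two-letter code, identifying one participant's arm identifies everyone's. Any analysis by adherence level, or any per-protocol set, built from those records could therefore break the mask.

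**The case against.** The strongest reply is that this is loose wording and not a failure of conduct. The schedule the biostatistician sees may carry coded arms. The person who generates the list may not be the person who analyses, with the word for blinded attached to the wrong role. Allocation is delivered through a central REDCap system, which is compatible with either reading. The article condenses a full protocol that is not shown, and key custody is a detail often left there. The primary outcome is a metabolic-cart measurement with blinded assessment, so an unblinded analyst could not change the recorded values. An adherence flag derived by someone else could be supplied in place of raw session data.

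Much of this stands. It rules out several stronger conclusions that a reader might draw:

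- *That the analyst was in fact unblinded.* The text shows an inconsistent access rule. It does not show that anyone used the access.
- *That the whole primary analysis is open to influence.* Most of it is fixed, as step 3 shows.
- *That blinding is the declared safeguard for the imputation choices.* No section says so. The article points to a later detailed analysis plan to guide the analyses.
- *That the absence of that plan aggravates the problem.* It was due before data collection ended, and its not yet existing is no defect.

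What the reply does not remove is the contradiction. The custody rule is an affirmative statement, not a gap left for a fuller document, and it conflicts with other affirmative statements in the same article.

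**Conclusion.** The point holds as an internal contradiction: the role claimed to be blinded is given the list that defines allocation, so statistician blinding is not assured by the plan as written. It is worth correcting because the remedy is specific, cheap and protects against bias.

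The size is modest and cannot be put as a number. In the primary analysis the exposure is mainly the choice of additional imputation covariates, and only if more than 5% of data are missing. Beyond that, it is the make-up of the per-protocol set. The one-arm session and platform data are a secondary matter, about the order of analyses and how they are labelled.

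The conclusion assumes that the biostatistician in the Randomization section is the one in the Blinding and Statistical Analysis sections, as the shared label suggests, and that the schedule shows the arms in clear. If either assumption is wrong, the blinding may be sound in practice and only the text needs repair.

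**What to change.** 1. Give custody of the schedule and the arm key to someone who does not analyse outcomes, such as an independent statistician or the data manager already mentioned under Data Collection and Management.
2. Remove the analysing biostatistician's access, and supply arm in the analysis file as a masked A/B code.
3. Align the Randomization, Blinding and Statistical Analysis sections: say who generates the schedule, who holds it and the key, and that this is not the analyst.
4. State that analyses using SCRAM session or platform data cannot be assumed blinded and are run after the blinded intention-to-treat analysis. Other workflows, such as a derived adherence flag, may serve, provided the claim made matches what is done.
5. If the access cannot be changed, drop the statistician-blinded label from the Abstract, the Design section and later reports. If the analyst has already opened an uncoded schedule, withdrawing access will not restore blinding; either another analyst is needed or the label goes.

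The cost is a change of access rights and a few sentences, with no effect on sample size, visits or participants. As of September 2019, 54 of 220 participants had been randomized (54/220 = 24.5%) and no interim analysis was planned, so at that stage the change could be made before any planned comparison of the arms.
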